**JUSTIFICATION**

HIV and cervical cancer are diseases that disproportionately affect women in resource-limited settings. The challenge of reducing cervical cancer in developing countries is too complex to be overcome simply by introducing current detection methods from resource-rich countries into resource-limited areas. The infrastructure—facilities, equipment, and personnel—and training required for conducting a proper examination, collecting a high-quality sample, transporting the sample to a well-trained lab and adequately performing the tests present significant barriers that hamper effective implementation of known screening technologies in low-resource settings. Novel strategies that have received attention recently include VIA and biomarker testing, for the benefits outlined above. VIA has been widely studied and even implemented in resource-limited settings, but has not yet been validated among HIV-infected women. Testing for p16^INK4a^ has never been carried out among HIV-infected women in resource-limited settings, where it could have the most impact. We will define the test characteristics and identify a cut-off value for “positive” in this population, using a biochemical assay which has the potential to be developed into a point of care test. In addition, we will compare p16^INK4a^ test performance with HR-HPV which is the most commonly known biomarker available. The high prevalence of HR-HPV among HIV-infected women in Kenya makes us believe that this test would have low specificity for CIN2/3.^79^ It is important to compare the two currently available biochemical tests side-by-side, to inform clinical decisions and development of screening strategies in this population.

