**Aim 2c: To investigate whether presence of increased baseline and follow-up levels of p16^INK4a^ in women with normal colposcopy or CIN1 is associated with increased risk of detecting CIN2/3 during one-year follow-up.** HIV-infected women enrolled in care at the FACES clinics in western Kenya who have had baseline p16^INK4a^ measurement, with normal colposcopy or CIN1 will be followed-up after one-year for repeat testing for p16^INK4a^, HR-HPV and colposcopy to compare rate of CIN2/3 between the two groups.

Hypothesis 2: The ROC curves for the biochemical assay for p16^INK4a^ will define a cut-off level for a positive result that will provide a sensitivity and specificity for CIN2/3 greater than those for HR-HPV testing in this population.

Hypothesis 2c: The risk of detecting CIN2/3 at one-year in women with normal colposcopy or CIN1 is increased in women with increased levels of p16^INK4a^ in cervical specimens at baseline and/or follow-up compared to women with normal or undetectable levels of p16^INK4a^.

**Aim 3: To measure and compare the quantity of HIV-1 RNA in the cervicovaginal secretions of women with cervical dysplasia to those with normal cervical exams.** We will measure and compare the presence and levels of cervicovaginal HIV-1 in women with biopsy-confirmed high-grade cervical dysplasia to those of women with no evidence of cervical disease. Cervical dysplasia will be defined as cervical intraepithelial neoplasia 2 or 3, or CIN2/3.

**Aim 3a: To determine the amount and duration of increased HIV-1 RNA shedding in the genital tract following cervical biopsy for suspected dysplasia.** We will measure the presence and levels of cervicovaginal HIV-1 in women prior to undergoing cervical biopsy and compare values to specimens taken on days 0, 2 and 7 following biopsy.

Hypothesis 3: Women with biopsy-confirmed CIN2/3 have higher odds of detectable genital HIV-1 viral load. Women undergoing biopsy will have an increase in genital HIV-1 RNA shedding that will return to baseline within 7 days post-procedure.

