HR-HPV DNA testing will be done at the MTM laboratories, under Dr. [name]’s direction. Testing will be done using fluid from the same collection vial as the p16 testing, and will be done using the Hybrid Capture 2 (Qiagen, Inc.) nucleic acid amplification test for 13 high risk HPV types 16, 18, 31, 33, 35, 39, 45, 51, 52, 56, 58, 59, 68. Results of the HPV DNA assay will be expressed as a ration of relative light units (rlu ratio) to the average of three positive controls, with 1.00 as the cut-off for test positivity. Internal quality assurance parameters and positivity cut-off parameters are determined by the manufacturer’s instructions. Positive HC2 tests will then be typed using reverse dot blot hybridization with recombinant HPV type-specific plasmids (Luminex, Inc). If the confirmatory test is negative, the amplimers will be cloned and sequenced. Only Hybrid Capture 2-positive samples confirmed by reverse dot blot hybridization or sequencing will be classified as HPV-positive.

The ARI-UCSF Laboratory of Clinical Virology, which will perform the HIV-1 RNA testing on genital specimens, is licensed by the State of California for clinical virologic and immunologic testing (CLIA # 05D0969871). The laboratory adheres to a comprehensive Quality Assurance program, and undergoes regular monitor visits from Laboratory Field Services and PPD, a contractor for the NIH/DAIDS, to ensure adherence to Good Clinical Laboratory Practices (GCLP) while supporting federally funded clinical trials.

Permits will be obtained through KEMRI prior to shipping specimens to UCSF and the MTM laboratories. We will continue to search for and work with local partners with laboratory capacity and expertise to run specimens for genital HIV-1 RNA. When genital HIV-1 RNA testing has been validated in local laboratories, we will run our specimens through those labs. We anticipate that this will be more efficient, less expensive and help to build local capacity. The p16^INK4a^ biochemical assays are not available at this time in Kenya, one of the reasons we are carrying out the work here. We are confident that the experience and results from this project will lead to further p16^INK4a^ testing and development of a point-of-care assay, work to be carried our by laboratories and clinical researchers within Kenya in the future.

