In addition to sensitivity and specificity, we will calculate the positive and negative predictive values of VIA. Studies have shown a PPV of VIA for CIN2/3 to range from 9-27% in HIV-negative women.^97, 100, 101^ To calculate the PPV in our study, we will divide the number of participants with a positive VIA by the number of participants found to have CIN2/3 on biopsy. VIA has been shown to have a negative predictive value (NPV) of 91-99.5% in HIV-negative women.^102^ To calculate the NPV, we will divide the number of participants with a negative VIA by the number of participants with no evidence of disease at colposcopy, either by visual impression or a negative biopsy result. Confidence limits for estimates of sensitivity, specificity, PPV and NPV will be exact, based on the binomial distribution.

Finally, we will compare the test characteristics between the two screening modalities using a McNemar’s test of proportions.

**Specific Aim 2**: To determine the cut-off value for the p16^INK4a^ biochemical assay that will provide the highest sensitivity and specificity for the detection of CIN2/3, we will construct a Receiver Operating Characteristic (ROC) curves using the results of the ELISA-based assay and the histology specimens. An ROC curve will allow us to plot the True Positive Rate (TPR) and the False Positive Rate (FPR) for various values of the p16^INK4a^ assay. As TPR is equivalent to the sensitivity of a test, and 1-FPR is the specificity, the graphical representation, as well as the calculated Area Under the Curve will allow us to determine the cut-off value for p16^INK4a^ to define a “positive test” with the highest sensitivity and specificity.

We will compare the absolute differences in sensitivity and specificity for detection of CIN2/3 of p16^INK4a^ and HR-HPV using the Mann-Whitney U test. The values of p16^INK4a^ will be determined from the ROC curves in Specific Aim 2. The sensitivity and specificity of the HR-HPV tests will be calculated as below:

- To calculate **sensitivity**, we will divide the number of women with a true positive test by the number of true positives plus the number of false negative HR-HPV testing.
- To calculate **specificity**, we will divide the number of participants with no disease diagnosed colposcopically (true negatives) by the number of true negative plus false positive HR-HPV tests.

Confidence limits for estimates of sensitivity and specificity will be exact, based on the binomial distribution.

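### The p16 cut-off criterion is undefined and the comparison with HR-HPV is not matched, so whether Hypothesis 2 is supported depends on the cut-off chosen

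*Protocol*

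**What the plan says.** - **Cut-off rule** (Data Quality and Management, Statistical Analysis, Specific Aim 2). The aim is the cut-off for the "biochemical assay that will provide the highest sensitivity and specificity for the detection of CIN2/3". The tools are the plotted ROC curve, "as well as the calculated Area Under the Curve will allow us to determine the cut-off value for p16^INK4a". No rule for trading one measure against the other is given.
- **Hypothesis 2** (Objectives). The ROC curves "will define a cut-off level for a positive result that will provide a sensitivity and specificity for CIN2/3 greater than those for HR-HPV testing".
- **Comparison for Aim 2a** (Statistical Analysis, Specific Aim 2). "We will compare the absolute differences in sensitivity and specificity for detection of CIN2/3" of the two tests. On the p16 side, "The values of p16^INK4a^ will be determined from the ROC curves in Specific Aim 2".
- **HR-HPV operating point** (Quality Assurance). Hybrid Capture 2 is read "with 1.00 as the cut-off for test positivity", and "Only Hybrid Capture 2-positive samples confirmed by reverse dot blot hybridization or sequencing will be classified as HPV-positive". That is one fixed point.
- **Expected HR-HPV performance** (Justification). High HR-HPV prevalence "makes us believe that this test would have low specificity for CIN2/3". No figure is given for its specificity or its sensitivity in this population.
- **Reuse of the cut-off.** Aim 2b takes its definition of a positive p16 from the pilot ROC curve. Aim 2c splits women by normal or increased p16 and does not define increased separately.

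**The concern.** Raising a threshold increases specificity and lowers sensitivity, so asking for the highest of both does not select a cut-off unless the two groups separate completely. The AUC averages over all thresholds and points to none. Two analysts following the text could choose different cut-offs from the same data.

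Hypothesis 2 is a statement about the curve: that it contains a cut-off better than HR-HPV on both measures. The planned analysis looks at one point on that curve. If that point is a balanced one and HR-HPV is sensitive but not specific, as the Justification leads one to expect for specificity, the two tests sit at different trade-offs. p16 could then show higher specificity and lower sensitivity, and Hypothesis 2 would be recorded as not supported although a qualifying cut-off exists elsewhere on the curve. The undefined rule also carries into Aims 2b and 2c.

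**Working it through.** **The plan's own figure.** The sample size section gives 90% power with 42 positive and 60 negative women for an AUC of 0.90 against 1.0, two-sided 0.05. Power = Φ(0.1/SE − 1.96). With a binormal variance, SE = 0.0297 at SD ratio 1 gives 92.1%, and SE = 0.0309 at SD ratio 0.75 gives 89.9%. The Hanley-McNeil variance gives 83.3% two-sided and 90.0% one-sided. The software inputs are not stated and standard variants come close, so 90% is not disputed. It concerns the AUC only and says nothing about the comparison with HR-HPV.

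**Inputs from the protocol.** p16 AUC 0.90. Women with CIN2/3: 140 × 0.57 ≈ 80. Women without: 60 + (140 − 80) = 120.

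**Assumptions.** Equal-variance binormal p16. HR-HPV specificity 55% (the protocol says only that it is low). HR-HPV sensitivity 70 to 95%. Tests independent given disease status. The balanced cut-off is the maximum of sensitivity + specificity − 1, chosen in the same data. Better means a higher point estimate.

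**Where the p16 curve lies.**
- Separation d = √2 × Φ⁻¹(0.90) = 1.414 × 1.2816 = 1.812.
- Balanced point: sensitivity = specificity = Φ(1.812/2) = Φ(0.906) = 0.818.
- p16 specificity at sensitivity s = Φ(1.812 − Φ⁻¹(s)).
- p16 sensitivity at specificity 55% = Φ(1.812 − 0.126) = 0.954.

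**Simulated chance that p16 is better than HR-HPV on both measures.**

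| HR-HPV sensitivity | True p16 specificity at that sensitivity (HR-HPV: 0.55) | At the balanced cut-off | At some cut-off on the curve |
|---|---|---|---|
| 70% | 0.90 | about 95% | about 100% |
| 80% | 0.83 | about 70% | about 99% |
| 85% | 0.78 | 42% | 97% |
| 90% | 0.70 | 17% | 86% |
| 95% | 0.57 | 2% | 49% |

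In every row the HR-HPV point lies below the true p16 curve, so Hypothesis 2 as worded is true in every row, though only just in the last (0.57 against 0.55). The balanced column drops below one half at an HR-HPV sensitivity of about 83%. Repeated runs agree to within about 4 percentage points.

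**Sensitivity to the assumptions.**
- HR-HPV specificity 0.40 to 0.60, AUC 0.90: balanced cut-off 66–69%, 42–44%, 17–18% and 2–3% at HR-HPV sensitivity 0.80, 0.85, 0.90 and 0.95. Any cut-off: 98–100%, 93–100%, 74–97% and 31–79%. The 31% belongs to specificity 0.60 at sensitivity 0.95, where the HR-HPV point really does lie above the p16 curve.
- AUC 0.95: balanced cut-off 91%, 73–76%, 43–46% and 10–13% at the same four sensitivities. It falls below one half above about 0.88.
- 42/60 women, AUC 0.90: balanced cut-off 64–66% at 0.80 and 22–24% at 0.90.

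**Why matching on sensitivity answers Hypothesis 2.** If p16 is strictly more specific at HR-HPV's sensitivity, a slightly lower p16 threshold gives higher sensitivity while specificity is still higher. On a continuous curve, such a cut-off is what Hypothesis 2 claims.

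**The case against.** **The selection index may be left to a SAP, and the ROC plot is named as well as the AUC.** This is partly right. A missing index alone would be a detail. But the protocol does state a rule, and that rule cannot be carried out as written. Nor can the AUC help choose the threshold, with or without the plot. The assay description mentions 16 U/mL when it reports precision, but does not adopt it as the study cut-off.

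**Comparing each test at its working threshold is a legitimate question, and the whole curve will be drawn.** This stands as a description of use in practice, and that comparison should be kept. It is a different question from Hypothesis 2, which asks whether any suitable cut-off exists.

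**A reader might infer that Hypothesis 2 will usually fail even when p16 is the better test.** The documents do not support that. It needs an HR-HPV sensitivity above about 83% (about 88% at AUC 0.95) and a balanced cut-off, and the protocol states neither. Its only indirect guide is that the Background calls VIA similar to HR-HPV in HIV-negative women, while Specific Aim 1 quotes VIA sensitivity of 60–86%. Most of that range lies where p16 would usually pass. It is a weak proxy for this population, but it does not favour the stronger claim. Read literally, Hypothesis 2 would be met in most simulated studies in all but the last row of the table.

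**Choosing and evaluating the cut-off in the same women favours p16.** Correct: sensitivity + specificity − 1 is inflated by about 0.03 with 80/120 women and 0.05 with 42/60. This works against the direction of the concern. It is a reason to put threshold selection inside the interval.

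**Conclusion.** The point holds in a limited form. The cut-off criterion is not usable as written, the AUC cannot supply the cut-off, and Aim 2a compares the tests at unmatched operating points. The conclusion on Hypothesis 2 therefore depends on an unspecified choice. At AUC 0.90, 80/120 women and HR-HPV specificity of 55%, that choice matters little at HR-HPV sensitivity of 70% (95% against 100%) and a great deal at 90% (17% against 86%).

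These figures rest on an equal-variance binormal curve, conditional independence, point-estimate comparisons and assumed HR-HPV values. They show that p16 can miss a true Hypothesis 2, not that it probably will. Since Hypothesis 2 is a research hypothesis, the outcome at risk is that it is not supported; nothing is rejected.

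**What to change.** 1. **Working cut-off for Aims 2b and 2c.** Name one criterion, for example the maximum of sensitivity + specificity − 1. Delete the statement that the AUC determines the cut-off, and keep the AUC as a summary of the curve.
2. **Hypothesis 2 in Aim 2a.** Prespecify one primary comparison: set the p16 threshold to HR-HPV's observed sensitivity and estimate the paired difference in specificity. Call the hypothesis supported only if the 95% interval excludes zero in favour of p16. Obtain the interval by a bootstrap over women that repeats the threshold selection in each resample.
3. **Secondary.** Report the reverse match (p16 sensitivity at HR-HPV's observed specificity) and the comparison at the working cut-off. Neither should be an alternative route to success. If p16 and HR-HPV are truly equal, p16 looks better on point estimates at one or other matched point in about 54% of simulated studies.

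The cost is protocol wording and a bootstrap program, with no new data. The downside is small: the interval is somewhat wider than with a fixed cut-off, because the matched threshold is itself estimated.

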We propose a ***cross-sectional*** study to evaluate this specific aim. Each participant will undergo a VIA or VILI with specimen collection for p16^INK4a^ and HR-HPV and colposcopy by a different clinician during a single clinic visit. The study clinician performing the colposcopy will be blinded to the results of the VIA or VILI. For women in the VILI arm, the colposcopy will be performed first in order to eliminate any interference with colposcopy interpretation from the iodine staining. Biopsy decisions will be made at the time of colposcopy, but deferred until after the VILI. Any woman with cervical lesions suspicious for dysplasia seen at the time of colposcopy will undergo biopsy. Colposcopy will be used as the reference standard for presence or absence of CIN2/3, with biopsy results being the final diagnosis when available. Women with a normal colposcopy without biopsy will be considered to have no disease.Specific Aims 1, 2, 2a and 2b)

We propose a **prospective cohort** study using a subset of women identified from the cross-sectional study in Specific Aims 1 and 2a to evaluate specific aim 2c during a one-year follow-up visit. We will recruit women for this follow-up study who participated in the pilot p16^INK4a^ ELISA study (Aim 2a) and had normal colposcopy or CIN1. In a single visit, each participant will undergo a VIA with specimen collection for p16^INK4a^ and HR-HPV followed by colposcopy and biopsy if needed.

We propose a ***case-control*** study to measure and compare the presence and quantity of HIV-1 RNA in the cervicovaginal specimens of women with biopsy-confirmed CIN2/3 (cases) and age-matched women without evidence of cervical disease as measured by negative VIA (controls). We will compute the odds ratio for HIV-1 detection and compare log transformed mean viral loads between cases and controls. (Specific Aim 3)

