**Single Follow-up visit**: Informed consent, VIA, colposcopy, and cervical specimen collection for HR-HPV, and p16^INK4a^ will take place during a single follow-up visit for women who previously underwent p16^INK4a^ testing and meet criteria for these specific aims. If indicated by abnormal findings at colposcopy, participants will undergo directed biopsy at the time of colposcopy for diagnosis of cervical dysplasia. No biopsies will be performed solely for study purposes.

Specific Aim 4 (7 study visits):

**Enrollment:** Women returning for their biopsy results who have CIN2/3 will be offered treatment with LEEP at this visit, as is the current clinic protocol at FACES. Recruitment and enrollment into the post-LEEP HIV-1 shedding study will take place at this visit. Women who meet eligibility criteria will be offered enrollment. Informed consent for this study will be obtained during this visit, and participants will be assigned a study ID number. A follow-up visit schedule will be made.

**Follow-up Visits at 1, 2, 4, 6, 8, 10 and 14 weeks:** Participants will undergo a brief interview followed by a sterile speculum exam with specimen collection for genital HIV-1 RNA.

Study measurements

Individual participant data, including demographic and clinical information will be collected from the paper medical record using study-specific data collection forms. Individual and de-identified aggregate data will be abstracted from the electronic medical record system (OpenMRS) in place at FACES. Participants will all be enrolled in FACES for care of their HIV disease; as part of this care, they have regular laboratory monitoring of CD4+ counts, hemoglobin levels and basic serum chemistries. Laboratory data for the study, apart from histology and HIV-1 RNA specimens, will be obtained from their FACES charts, and will not be collected independently for the study.

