**Predictor Variables**

Predictor demographic variables will include participant age, gravidity, parity, history of cervical cancer screening, marital status and number of current and previous sexual partners. Clinical predictors will include WHO status of HIV disease, CD4+ count, opportunistic infections, previous sexually transmitted infections and current use of anti-retroviral therapy.

For Specific Aim 2c, predictor variable will be p16^INK4a^ ELISA levels found during initial screening. The other variables above will be collected and treated as potential confounders.

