**Specific Aims 2c:** To compare the rate of detecting CIN2/3 at one-year follow-up between women with normal or increased levels of p16^INK4a^ at baseline, we will use the Pearson’s chi-square test to investigate any significant differences in the proportions. Based on our sample size calculations, we aim to have 80 percent power with a two-sided alpha of 0.05. To compare the rates of developing CIN2/3 at one-year follow-up between women with persistently elevated p16^INK4a^ compared to those with only one elevated measurement, we will also use the Pearson’s chi-square test to look for statistically significant differences in proportions of CIN2/3 in the two groups.

**Specific Aim 3:** To compare the presence and magnitude of HIV-1 genital shedding between women with and without cervical dysplasia we will compute the odds ratio of HIV-1 detection in genital secretions with 95% confidence intervals. Multivariate analyses will be performed using logistic regression to control for demographic and clinical confounders. Potential confounders include WHO stage of HIV disease, CD4+ count, plasma HIV-1 viral load, opportunistic infections, previous STIs and current use of anti-retroviral therapy.

**Specific Aim 4:** The goal of specific aim 4 is to determine the magnitude and duration of increased HIV-1 genital shedding that occurs after treatment with LEEP. Observed time trends in log copies of genital HIV-1 RNA will initially be evaluated via exploratory analyses of longitudinal measures based on scatter plot smoothing methods. Results will allow us to assess possible nonlinearities in trends, as well as investigate differences in results between subgroups of interest. The subgroups we are looking at include participants on HAART and who have CD4+ counts below 200. Further analyses will focus on estimation of post-LEEP changes from baseline levels in log copies of HIV-1 RNA using linear mixed effects regression methods. The primary predictor will be time on study (measured in weeks post-treatment). Initial models will include separate coefficients for each week of observation post-treatment (2, 4, 6, 10 and 14). Hypothesis 2 will be addressed directly via tests constructed about these coefficients. We will also explore the effect on results of adjustment for selected covariates, including demographic characteristics and baseline descriptors of participant health status.

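### Aim 2c's second chi-square and the follow-up part of Hypothesis 2c use p16 sampled at the diagnostic visit as a predictor of that visit's CIN2/3, so neither can be read as progression risk

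*Protocol*

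**What the plan says.** Aim 2c follows women from the p16 pilot whose baseline colposcopy was normal or showed CIN1, and looks for CIN2/3 one year later.

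- **Timing.** Study Design states: "In a single visit, each participant will undergo a VIA with specimen collection for p16^INK4a^ and HR-HPV followed by colposcopy and biopsy if needed". The visit schedule for Aim 2c agrees: "cervical specimen collection for HR-HPV, and p16^INK4a^ will take place during a single follow-up visit". No p16 sample is planned between baseline and that visit.
- **Predictor.** The Predictor Variables section names, for Aim 2c, the p16 "ELISA levels found during initial screening".
- **Hypothesis.** Hypothesis 2c is wider. It concerns raised p16 "in cervical specimens at baseline and/or follow-up compared to women with normal or undetectable levels". The text of Aim 2c likewise refers to both baseline and follow-up levels.
- **Analysis.** Statistical Analysis for Aim 2c gives two tests. The first compares CIN2/3 by baseline p16 only. The second compares rates of developing CIN2/3 in women whose p16 is persistently elevated "compared to those with only one elevated measurement", and for this "we will also use the Pearson’s chi-square test to look for statistically significant differences in proportions of CIN2/3 in the two groups".

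**The concern.** With two samples, persistent elevation can only mean raised at baseline and raised again at the visit where CIN2/3 is diagnosed. The Background presents p16 as over-expressed in HPV-transformed cells and closely tied to existing CIN2/3. On that premise, a lesion present at the visit raises the follow-up p16, and the outcome helps decide which group a woman joins. Taking the swab shortly before the colposcopy does not make it a prospective measurement.

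The comparison group adds a second problem. Women with one elevated value are of two kinds: raised then normal, where CIN2/3 should be rare, and normal then raised, where new CIN2/3 should collect. Their pooled risk depends on the mix.

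At stake is the interpretation. A difference in either direction could be reported as evidence about p16 and progression when it reflects concurrent detection and group mix.

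**Working it through.** The plan gives no figure for this comparison, so there is none to reproduce. The check asks how the second test behaves when baseline p16 has no prospective value.

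**Inputs from the protocol**
- Women available: 55 CIN1 + 190 normal = 245 (sample size text, Aim 2c). Complete follow-up is assumed.
- About half of each group had raised p16 at baseline (same place).
- Two-sided alpha 0.05 (Statistical Analysis, Aim 2c).

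**Assumptions, not stated in the protocol**
- One-year CIN2/3 risk r = 5% to 10%. The Aim 1 analysis text assumes a 7% screening prevalence, which is only a stand-in.
- Follow-up p16 is raised in s = 90% of women with CIN2/3.
- Follow-up p16 is raised in 50% of women without CIN2/3, carrying forward the baseline share.
- q is the share of disease-free women raised at baseline who are still raised at one year. To hold 50% overall, the share newly raised among those normal at baseline is 1 − q.

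**Group risks when baseline p16 is independent of the outcome**
- Persistent: rs / [rs + (1 − r)q]
- Only one elevated: r / [r + 2(1 − r)(1 − q)]

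For r = 10%:
- q = 0.50: persistent 0.09/(0.09 + 0.45) = 16.7%; one elevated 0.10/(0.10 + 0.90) = 10.0%
- q = 0.64: persistent 0.09/(0.09 + 0.576) = 13.5%; one elevated 0.10/(0.10 + 0.648) = 13.4%
- q = 0.80: persistent 0.09/(0.09 + 0.72) = 11.1%; one elevated 0.10/(0.10 + 0.36) = 21.7%

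For r = 5%:
- q = 0.50: 0.045/(0.045 + 0.475) = 8.7% against 0.05/(0.05 + 0.95) = 5.0%
- q = 0.80: 0.045/(0.045 + 0.76) = 5.6% against 0.05/(0.05 + 0.38) = 11.6%

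The two risks are equal when 2s(1 − q) = q, that is q = 2s/(1 + 2s) = 1.8/2.8 = 0.64, whatever r is. Below that the persistent group looks worse; above it the one-elevated group does.

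**Rejection rate of the uncorrected Pearson chi-square** (simulation, 245 women, same null)

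| Still raised, disease-free (q) | Rejection for r = 5% to 10% | Direction |
|---|---|---|
| 50% (no stability) | about 17% to 27% | toward persistence |
| 64% | about 5% | balanced |
| 80% | about 27% to 43% | against persistence |

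The baseline-only chi-square rejects in about 5% of runs, as it should.

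**Mixture in the one-elevated group** (r = 10%, q = 0.50)
- Normal then raised: 0.09/(0.09 + 0.45) = 16.7%
- Raised then normal: 0.01/(0.01 + 0.45) = 2.2%

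**Hypothesis 2c wording.** Under the same null and inputs, all women raised at follow-up have 16.7% CIN2/3 and all women not raised have 2.2%. That contrast is concurrent accuracy only.

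**The case against.** The strongest objection concerns direction. A reader might infer that persistent elevation is bound to look predictive. That follows only if, in disease-free women, follow-up p16 is unrelated to the same woman's baseline p16. The documents do not say how stable p16 is, and moderate stability removes the excess or reverses it. This objection stands, and the point is framed accordingly.

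A reader might also expect much larger error rates. With disease-free positivity of 30% or 20%, no stability and 10% CIN2/3, rejection reaches about 67% and 88%. The protocol does not support those inputs: about half of these women, none of them with CIN2/3, had raised p16 at baseline. The 82–84% specificity in the Background belongs to a cytology and biopsy scoring system, not to this ELISA.

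Nor is Aim 2c as a whole invalid. The first chi-square uses baseline p16, agrees with the Predictor Variables section and is sound.

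Two further arguments carry less weight. Aim 2c speaks of association with detecting CIN2/3, which could include concurrent association, but the analysis text speaks of developing CIN2/3 and Hypothesis 2c of risk at one year. The sample size text calls the study exploratory. That lowers the priority and excuses low power, but it does not make an outcome-dependent grouping interpretable. A separate analysis plan would not settle the matter either, because the protocol itself fixes the groups, the test and the hypothesis.

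**Conclusion.** The point holds for the second chi-square and for the follow-up part of Hypothesis 2c, and for nothing else in Aim 2c. Both use a measurement concurrent with the outcome as if it preceded it, and both conflict with the section naming initial-screening p16 as the predictor.

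The conclusion that the comparison cannot be read as progression risk rests on the visit schedule and on the protocol's own premise that p16 marks existing CIN2/3. If p16 had no concurrent association either and were unstable, the test would behave normally. The error rates in the table are illustrations under the listed assumptions. What they support is that the bias can run either way and that its direction turns on a quantity the documents do not give. Severity is should-fix: a secondary comparison in an aim the protocol calls exploratory, with the main baseline comparison intact.

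**What to change.** 1. Keep baseline p16 as the only predictor for the one-year risk claim. Delete the and/or follow-up wording from Hypothesis 2c, and bring the Aim 2c text and Statistical Analysis into line with Predictor Variables.
2. Replace the persistent-versus-one chi-square with a cross-sectional report of the sensitivity and specificity of follow-up p16 for CIN2/3 at that visit.
3. If the four baseline-by-follow-up patterns are shown, keep raised-then-normal and normal-then-raised separate. Label the display concurrent and descriptive, and draw no risk conclusion from it.

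The cost is a change of wording in the aim, the hypothesis and one analysis paragraph; no new data or visits are needed. The downside is that the persistence claim is given up, and two samples with the second at diagnosis cannot support it.
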